### Sample size

A standard deviation for the OKS of 8, an attrition rate of 15%, and a clinically important difference of 3 points were determined from a preliminary feasibility study. However, because the intervention is very inexpensive and low-risk it could be argued that a smaller difference than 3 may still be meaningful. Assuming a more conservative attrition rate (20%) than was observed in the feasibility trial and powering at 80% to detect a 1-point difference we need to recruit and randomise 2515 participants. We have decided to round this to 2600. Furthermore, the power of the study does not include the influence of covariates (e.g. baseline test score), which will correlate with the outcome scores and provide increased power from the adjusted regression analyses.

### Recruitment

All patients scheduled for TKA who are deemed eligible by their surgical team will be mailed information or given information on the trial at a pre-operative visit. Patients will be given sufficient time to accept or decline involvement. Patients will be given the opportunity to discuss the trial with research staff or their treating surgical team prior to their surgery. Following confirmation of eligibility, written informed consent will be obtained by research staff prior to surgery. Participants will be free to withdraw from the study at any time without affecting their routine care.

Strategies for achieving adequate participant enrolment to reach the target sample size include seeking advice from our patient representatives, sharing best practice with our Research Nurses, and regular discussion with our Principal Investigators (PIs).

Site staff will be provided with training at the site initiation visits to ensure adherence to the delivery of the interventions in the trial. During the trial, training and reminders will be implemented using e-mail bulletins, and discussion with the PIs and with Research Nurses. In addition, the Trial Co-ordinators will provide support and guidance to staff when required (e.g. when new staff join or replace existing site staff) and will seek clinical guidance from the Chief Investigator (CI) when necessary.

### Randomisation

Simple, equal randomisation without stratification or blocking will be used to generate the treatment allocation schedule. As the sample size of the trial exceeds 200 there is no loss of statistical efficiency compared with using more complex (restricted) randomisation methods [9].

When patients have given consent and their baseline forms have been completed, the Research Nurse or recruiting clinician will randomise them using the York Trials Unit’s (YTU) secure, web-based randomisation service. Patients will be allocated 1:1 to receive either compression bandaging or standard care (wool and crepe) bandaging, therefore ensuring allocation concealment and immediate unbiased allocation. Patients will be informed of their allocations as will the clinician managing each patient.

### Data management

Paper case report forms (CRFs) will be used to record all the information required from the protocol with the following exceptions: demographic, comorbidity, and complications data will be downloaded from Patient Administration Systems (PAS) at each site; pain scores will be collected from participants via SMS message where they have agreed to be contacted via this means; and Patient-Reported Outcome Measures (PROMs) at baseline and 6 months post-surgery (OKS and EQ-5D-3 L) will be obtained via the NHS Digital’s PROMS project (https://www.england.nhs.uk/statistics/statistical-work-areas/proms/) and reported via participating sites to YTU.

All data will be completely anonymised for the purposes of analysis and any subsequent reports or publications. For the purposes of ongoing data management, once randomised, individual participants will only be identified by trial identification numbers to maintain confidentiality.

All paper records will be kept in locked locations. All consent forms will be secured safely in a separate compartment of a locked cabinet. Essential trial documentation (i.e. the documents which individually and collectively permit evaluation of the conduct of a clinical trial and the quality of the data produced) will be kept with the Trial Master File and Investigator Site Files. At the end of the study, paper copies of data will be securely archived by participating sites and the University of York for a minimum of 5 years. Electronic data will be stored indefinitely.

Once YTU has completed the analysis and published all intended scientific journals, data will be made available for other researchers for secondary analysis upon request. Requests for access to data will be reviewed by the CI and study sponsor.

### Statistical analysis

A detailed analysis plan will be agreed with the combined Trial Steering Committee (TSC) and Data Monitoring and Ethics Committee (DMEC) at an early stage of the study, before all of the data have been collected. Any subsequent amendments will be clearly stated and justified. Analyses will be conducted following the principles of intention-to-treat (ITT) with outcomes analysed according to the patients’ original, randomised group irrespective of deviations based on non-compliance, and significance tests will be two-sided at the 5% level, unless otherwise stated.

The primary analysis will compare total OKS scores between the treatment groups at 12 months using a covariance pattern mixed model incorporating outcome data at 6 and 12 months, adjusting as fixed effects for age, gender, baseline score, time point, treatment group, and a treatment group-by-time point interaction, and hospital site as a random effect. Treatment effects in the form of an adjusted mean difference will be presented with an associated 95% confidence interval (CI) and *p* value for both time points (6 and 12 months). The primary end-point will be the treatment effect estimate at 12 months, while the treatment effect at 6 months will serve as a secondary outcome. Pain score (at 10 days, 4 weeks, and 12 months) will be analysed similarly.

The proportion of participants who, within 30 days of surgery, 1) return to theatre, 2) are readmitted to hospital, 3) experience a PE requiring hospitalisation, and 4) experience a DVT requiring hospitalisation will be compared between the two groups using mixed effects logistic regression models, adjusting for age and gender as fixed effects, and hospital site as a random effect. The treatment effect in the form of an odds ratio will be presented with an associated 95% CI and *p* value.

Length of hospital stay in days will be analysed via a mixed effect Poisson, or negative binomial, regression model as appropriate, adjusting for age and gender as fixed effects, and hospital site as a random effect. An incidence rate ratio, 95% CI and *p* value will be provided.

### Interim analysis

There are no planned interim analyses for the trial or stopping guidelines.

### Cost-effectiveness analysis

An economic analysis will be undertaken to determine the cost-effectiveness of compression bandages versus standard bandages following TKA. This will take the form of a cost-utility analysis, thereby incorporating the impact on patients’ health-related quality of life. The analysis will be conducted from the perspective of the UK NHS and Personal Social Services (PSS), in line with NICE recommendations.

Health benefits for the economic evaluation will be measured in terms of quality-adjusted life years (QALYs). The EuroQol EQ-5D-3 L will be used to obtain utility values for use in the cost-utility analysis. QALYs will be generated for each patient based on the area under the curve approach (Richardson G). EQ-5D data will be collected at baseline (pre-operatively) and 6 months post-operatively (both collected routinely via the National PROMS programme) and at 12 months (via a 12-month follow-up participant questionnaire). At baseline and 12 months, in addition to the EQ-5D-3 L, we will also collect EQ-5D-5 L data to enable a mapping exercise and to utilise the updated -5 L version of the EQ-5D. An analysis of the order in which the EQ-5D-3 L and EQ-5D-5 L appear in the 12-month follow-up questionnaire will be undertaken to assess ordering effects associated with the presentation of the two EQ-5D versions.

Costs will be assessed for the two groups; healthcare resource use data will be collected. Specifically, primary care resource use (i.e. General Practitioner (GP), nurse, physiotherapist, occupational therapist visits) and resource use in the hospital setting (i.e. hospital outpatient appointments, inpatient stays, day cases, and accident and emergency admissions) will be obtained using patient self-reported data from the 12-month follow-up questionnaire. Data obtained via routine data collection methods (e.g. outpatient visits) may also feed into the economic analysis if available. Unit costs will then be applied to the quantities of resources utilised, for example using NHS Reference Costs (Department of Health) and Unit Costs of Health and Social Care [10]. In addition, product/intervention costs such as bandages/equipment will be costed and information relating to complications will be incorporated for the two groups. Information on patients’ return to work/activities will also be collected.

The within-trial analysis will use regression methods to generate estimates of mean costs and health outcomes (i.e. QALYs), allowing for correlation between cost and outcome data, and will adjust for covariates. The results will be presented in terms of incremental cost-effectiveness ratios (ICERs), specifically the incremental cost per QALY. Future costs and outcomes will not be discounted due to the trial follow-up not exceeding 12 months. Multiple imputation methods will be used to handle missing data where needed [11]. Cost-effectiveness acceptability curves will be produced to explore the probability that compression bandages will be cost-effective at different cost-effectiveness thresholds [12]. Uncertainty will also be explored via sensitivity analysis to investigate the impact of underlying assumptions of the analysis and key cost drivers in terms of the cost-effectiveness results.

### Adverse event management

Adverse events related to the participant’s trial-related compression bandaging up to 1 month after their knee operation will be collected. Adverse events considered to be a consequence of the surgery will not be collected or reported in the context of this study. Symptoms relating to possible complications of surgery, inter-current illness, or any inpatient episode within 30 days of surgery will be collected. Other than for fatalities, this procedure does not apply to any other adverse events which may occur during the trial which are unrelated to the trial procedures.

The severity and likely relationship of any adverse events will be documented by the designated site clinician. An event is defined as ‘related’ if the event was due to the administration of any research procedure, whereas an ‘unexpected event’ is defined as a type of event not listed in the protocol as an expected occurrence. The relatedness of an event will be reviewed by the Chief Investigator and the Trial Steering Committee. Serious adverse events that are confirmed to be related to the research and are unexpected will be reported to the Research Ethics Committee (REC). All adverse events will be routinely reported to the Trial Management Group (TMG) and sponsor. The combined TSC/DMEC will be responsible for reviewing related and unexpected serious adverse events.

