### Quality control

Northumbria Healthcare NHS Foundation Trust has agreed to be the lead sponsor for this project and take overall responsibility for the quality of study conduct. This study will be fully compliant with the Research Governance Framework and MRC Good Clinical Practice Guidance.

A rigorous programme of quality control will be undertaken. The day-to-day management of the trial will be the responsibility of the Trial Co-ordinator based at York Trials Unit. Regular meetings with the Trial Management Group will be held and will monitor adherence to the trial protocols at the trial sites.

Due to the low-risk nature of this study, approval will be sought from the funders to set up one Independent Steering and Monitoring Committee to undertake the roles traditionally undertaken separately by the TSC and the DMEC. This committee will comprise of an Independent Chair who will be a surgeon with expertise in knee replacement surgery, a statistician, a member of the Patient Group, the Chief Investigator, and Trial Coordinator/Manager. Other study collaborators may also attend the meeting. The independent members of the committee will be allowed to see unblinded data. The role of this committee will include the review of all serious adverse events which are thought to be treatment-related and unexpected. The committee will meet at least annually or more frequently if the committee requests.

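### The adverse event section names only the compression bandage and contradicts itself on surgical complications, so harms short of hospital care may be recorded unevenly between arms

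*Protocol article*

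**What the plan says.** The rules are in the protocol article under Adverse event management, mostly in consecutive sentences.

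- Scope: events related to the participant's "trial-related compression bandaging up to 1 month after their knee operation will be collected". The control bandage is not mentioned.
- Exclusion: "Adverse events considered to be a consequence of the surgery will not be collected or reported in the context of this study".
- Inclusion, in the next sentence: "Symptoms relating to possible complications of surgery, inter-current illness, or any inpatient episode within 30 days of surgery will be collected".
- Limit: "Other than for fatalities, this procedure does not apply to any other adverse events which may occur during the trial", where the events meant are those unrelated to trial procedures.
- Attribution: "The severity and likely relationship of any adverse events will be documented by the designated site clinician". The definition that follows is "An event is defined as ‘related’ if the event was due to the administration of any research procedure".

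Under Randomisation the article adds: "Patients will be informed of their allocations as will the clinician managing each patient".

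Harms are also covered elsewhere. Secondary outcomes lists return to theatre and readmission for any reason, and PE and DVT needing inpatient care, all within 30 days and for each group. Data management takes complications data from the hospitals' patient administration systems. Statistical analysis compares these four outcomes between arms by mixed effects logistic regression.

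**The concern.** A fair comparison of harms needs the same rule for what is recorded in each arm, applied without regard to allocation. Three features of this section work against that.

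1. The opening sentence covers events linked to a treatment that only one arm receives.
2. The next two sentences give opposite instructions on surgical complications. Sites have to choose between them, and about 26 sites may choose differently.
3. Under the exclusion sentence, attribution decides whether an event enters the record at all. That judgement is made at site in an open trial, and nothing in the article says that the designated clinician is masked.

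At stake are the milder harms that a bandage could plausibly cause. The Intervention group section foresees them, since it allows early removal for marked discomfort or an adverse occurrence. The Sample size section relies on the treatment being low-risk when it argues that a difference smaller than 3 points may still matter. An even record of minor harms would support that argument when the result is reported.

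**Working it through.** The article gives no adverse event rate and plans no test on events reported under this section, so the main check is a reading of the text. The table follows four kinds of event through the rules. S1, S2 and S3 are the scope, exclusion and inclusion sentences in the order above.

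| Event within 30 days | Compression arm | Wool and crepe arm |
|---|---|---|
| Skin, pressure or discomfort problem from the bandage, no hospital care | Collected under S1 | Not named in S1; S3 helps only if it is treated as a symptom of a surgical complication |
| Wound or nerve problem that could be due to bandage or operation, no hospital care | Attributed to the bandage: collected under S1. Attributed to surgery: S2 says no, S3 says yes | S1 not available; attributed to surgery: S2 says no, S3 says yes |
| Return to theatre, readmission, hospitalised PE or DVT | Counted as a secondary outcome | Counted as a secondary outcome |
| Death | In scope | In scope |

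**Row 1.** The rule differs by arm on its face. The definition of a related event, which refers to any research procedure, does not clearly close the gap. It classifies events rather than saying which are collected, and the control bandage is standard care, so whether it counts as a research procedure is open.

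**Row 2.** In the compression arm there are two possible attributions, and one leads to certain collection. In the control arm only the contradictory pair S2/S3 applies. The same clinical event can be kept in one arm and dropped in the other.

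**Rows 3 and 4.** No attribution is needed, so the wording problem does not reach them.

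**Can the row 3 outcomes be compared in practice?** This is an illustration only. Inputs: 2600 patients allocated 1:1, so about 1300 per arm (2600 / 2); two-sided 5% level; 80% power; complete 30-day data assumed; control rates assumed, because none are given. For control rate p, intervention rate q and mean rate m = (p + q)/2, the number needed per arm is

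n = [1.96 √(2m(1−m)) + 0.842 √(p(1−p) + q(1−q))]² / (q − p)².

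For p = 1% and q = 2.45%: m = 0.01725, and n = (0.361 + 0.155)² / 0.0145², about 1265, which is within 1300. Searching upwards in steps of 0.05 percentage points, the smallest detectable rates are:

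| Assumed control rate | Detectable intervention rate | Ratio |
|---|---|---|
| 0.5% | about 1.65% | 3.3 |
| 1% | 2.45% | 2.45 |
| 2% | 3.9% | 1.95 |
| 5% | 7.7% | 1.54 |

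So the hospital-level harms can be compared, although for rare events only large relative differences would be detected.

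**The case against.** The strongest reply is that most of the important harms are already protected.

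- **A reader might infer that adverse events are collected only if caused by the compression bandage.** The section does not support this. It also takes in symptoms of possible surgical complications, intercurrent illness, any inpatient episode within 30 days and deaths.
- **A reader might infer that harms cannot be compared between arms.** This does not follow. Four 30-day outcomes are defined for both groups, do not depend on attribution to the bandage and have a stated between-arm analysis. A PE or DVT needing inpatient care cannot be lost by being called surgical, nor can a wound or nerve problem that leads to readmission or reoperation.
- **A reader might put a number on the bias.** With 1300 per arm and a true rate of 1% in both arms, strict application of the opening sentence would give 1300 × 0.01 = 13 events against 0. That is circular: the zero is assumed, the inclusion sentence applies to both arms, and no test of these events is planned.
- **A reader might infer that the oversight committee sees only events already judged related and unexpected.** The text is "The role of this committee will include the review of all serious adverse events which are thought to be treatment-related and unexpected", and the word include leaves the list open. The committee also takes on the roles usual for a data monitoring committee, its independent members may see unblinded data, and relatedness is itself reviewed by the Chief Investigator and the steering committee. Which tables it sees belongs in a charter.

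All four replies stand. They leave rows 1 and 2 of the table untouched. Central review of relatedness can act only on what a site has reported, and the article states no other clear route for bandage-type events that stop short of hospital care. The article condenses a longer protocol, but this is a contradiction in text that is present, not a detail left out.

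**Conclusion.** The concern holds for the adverse event reporting stream and no further. As written, the section ties bandage-related collection to one arm's treatment and gives opposite instructions on surgical complications. Counts of skin, nerve, wound and discomfort events that do not lead to theatre, readmission or a hospitalised PE or DVT may therefore not be comparable by arm.

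The direction is uncertain. Minor bandage problems may be over-represented in the compression arm, while real compression harms that look surgical may be dropped. The size cannot be derived from the article.

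This rests on two assumptions: that sites follow the wording literally, and that the clinician who attributes events knows the allocation. The article states the latter for the managing clinician and says nothing to the contrary for the designated one. The primary outcome and the four 30-day hospital outcomes are not affected.

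**What to change.** Amend the Adverse event management section and the matching case report form guidance:

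1. Replace the reference to compression bandaging with the allocated trial bandage (compression or wool and crepe).
2. Reconcile the exclusion and inclusion sentences into one collection definition that applies in both arms to 30 days, whatever the attributed cause.
3. Record relatedness as a separate field, so that it describes an event and does not decide whether the event is kept.
4. Report these events by randomised arm.

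The cost is a reworded section, revised guidance and slightly more site reporting. The gain is limited by timing. With 2150 of 2600 patients randomised by July 2018, at most 2600 − 2150 = 450 patients (450 / 2600 = 17%) were still to enter. Earlier patients can be covered only from existing records, which may not hold minor events. The report should state that limit beside the counts and avoid reading a between-arm difference in them as an unbiased estimate.

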### Quality control

Northumbria Healthcare NHS Foundation Trust has agreed to be the lead sponsor for this project and take overall responsibility for the quality of study conduct. This study will be fully compliant with the Research Governance Framework and MRC Good Clinical Practice Guidance.

A rigorous programme of quality control will be undertaken. The day-to-day management of the trial will be the responsibility of the Trial Co-ordinator based at York Trials Unit. Regular meetings with the Trial Management Group will be held and will monitor adherence to the trial protocols at the trial sites.

Due to the low-risk nature of this study, approval will be sought from the funders to set up one Independent Steering and Monitoring Committee to undertake the roles traditionally undertaken separately by the TSC and the DMEC. This committee will comprise of an Independent Chair who will be a surgeon with expertise in knee replacement surgery, a statistician, a member of the Patient Group, the Chief Investigator, and Trial Coordinator/Manager. Other study collaborators may also attend the meeting. The independent members of the committee will be allowed to see unblinded data. The role of this committee will include the review of all serious adverse events which are thought to be treatment-related and unexpected. The committee will meet at least annually or more frequently if the committee requests.

## Discussion

### Protocol modifications

Important protocol modifications are those that are likely to affect, to a significant degree: the safety, physical or mental integrity of the subjects of the study; the scientific value of the study; or the conduct or management of the study. These substantial amendments will be submitted to the Health Research Authority (HRA) and REC for approval, having first been agreed with the Sponsor and TMG. Minor modifications to the protocol will be agreed with the TMG before submission for approval to the HRA. All amendments will be implemented in the NHS organisations in compliance with HRA guidance. Trial participants will be written to, if necessary, to explain any changes. All amendments, whether substantial or not, will be listed in the published Final Report.

